### Statistical analysis

The primary end-point (Pap test compliance) will be coded as a binary variable. Evaluation of the success of the intervention is based only on Pap test compliance at follow-up. Chi square tests of 2 X 2 tables (compliance Yes/No by arm Control vs. High or Low intensity intervention) will be employed to assess whether intervention arms affects the probability of compliance at follow-up. We will randomize about 600 women (anticipated 200 per arm to each of 3 arms; control, low intensity intervention, high intensity intervention) into the study, which will allow for 10% attrition. Separate analysis will be conducted to compare the high intensity arm to the control arm and the low intensity arm to the control arm, and subsequent analysis will include comparing the low intensity arm to the high intensity arm as well as adjustment of the primary analysis by potential confounding characteristics such as race and age, to account for potential biases in the randomization.

Additional secondary analysis will include evaluating the effect of contact from a patient navigator to women who receive an abnormal Pap smear. All participants seen at the study clinics during the course of the study who receive an abnormal Pap smear (intervention population) will receive a contact from the patient navigator. These women will be compared to women who received an abnormal Pap smear at the same clinics between 180 and 90 days prior to the start of the study when no navigator calls were made (control population) as determined by medical records. The outcome measure will be determination of follow up for an abnormal Pap smear within 90 days of initial contact by the clinic. We will compare length of time from initial diagnosis to attendance at the clinic for recommended follow-up in the participants who have been contacted by the patient navigator, vs. the control population

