**Methods/design:**

A parallel randomized-controlled trial of 600 Hispanic women aged 21–64, who are non-compliant with Papanicolau (Pap) test screening guidelines. Participants will be randomized using block randomization to (1) a control arm (usual care); (2) a low-intensity information program, consisting of a Spanish-language video that educates women on the importance of cervical cancer screening; or (3) a high-intensity program consisting of the video plus a *‘promotora’* or lay-community health educator-led, home based intervention to encourage cervical cancer screening. Participants who attend cervical cancer screening, and receive a diagnosis of an abnormal Pap test will be assigned to a patient navigator who will provide support and information to promote adherence to follow-up tests, and any necessary surgery or treatment. Primary endpoint: Participants will be tracked via medical record review at community-based clinics, to identify women who have had a Pap test within 7 months of baseline assessment. Medical record reviewers will be blinded to randomization arm. Secondary endpoint: An evaluation of the patient navigator program as a method to improve adherence and reduce time to follow-up among participants who receive an abnormal Pap test result. An additional secondary endpoint is the cost-effectiveness of the two different intensity intervention programs.

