The aims of the Cervical Cancer Screening and Adherence to Follow-up Among Hispanic Women study are threefold: (1) to determine the effect of two different intensity, culturally appropriate information based interventions on Pap test utilization, vs. control; (2) to determine whether a patient navigator program can improve adherence to follow-up after a diagnosis of an abnormal Pap test, in a sample of Hispanic women in Yakima and Franklin counties of Washington (WA) State, US; and (3) to assess the cost-effectiveness of each of the intervention programs.

The study will be implemented with the aid of the two community based partners, the Yakima Valley Farm Workers’ Clinic (YVFWC) which operates a network of 13 federally qualified health center clinics in Eastern Washington specializing in the delivery of primary care services to low-income Latinos; and the Breast, Cervical, and Colon Health Program of the Yakima District (BCCHP), a federally funded aid program, administered through the Washington State Department of Health, which provides assistance and resources for women to undergo Pap tests, and for women who receive a diagnosis of an abnormal Pap test.

BCCHP and YVFWC will work with the study investigators to identify women who are non-compliant with Pap testing to monitor uptake of Pap test screening among randomized women via medical record review, and to develop and pilot test a patient navigator program to improve adherence and reduce time to follow-up after an abnormal Pap test.

To aid with issues regarding cultural relevance, a community advisory board was appointed and regular meetings are scheduled between the investigators and community members.

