### Secondary outcomes

As part of the reason for high cervical cancer mortality rates among Latinas is the lack of recommended follow-up, for abnormal Pap tests, a secondary outcome is compliance with such recommendations. The approach being used is a patient navigator approach where a *promotora* works closely with the participant to encourage her to attain the recommended follow-up.

The first patient navigator program was introduced by [name], in a successful effort to increase access to early effective medical care for breast cancer patients at the Harlem Hospital in New York City [21]. Patient navigators aid patients in navigating barriers to receiving care, such as competing demands of work, family responsibilities, transportation and childcare. In addition, Hispanic women may experience specific barriers to care such as culturally specific health beliefs, immigration status and language barriers that would make obtaining and completing optimal care more difficult [22].

Following formative work interviewing Hispanic women in the Yakima Valley who had received abnormal Pap test results, we developed a culturally-appropriate patient navigator program. Any participant, who receives a diagnosis of an abnormal Pap test after their initial cervical cancer screening, will be offered the services of a patient navigator. The patient navigator will contact the participant and guide them through potential barriers to care, such as transportation, childcare, financial impediments and cultural or linguistic barriers. Patient navigator contact will cease when the participant has successfully completed follow-up diagnostic care or treatment. Patient navigators will be selected from the different community partner organizations to work collaboratively and ensure sustainability of the program. Training will provide basic knowledge on cervical cancer screening as well as communicational skills. The secondary outcome will measure the time between diagnosis of the first abnormal Pap test, and attendance at the clinic for follow up. Elapsed time in participants assigned to a patient navigator will be compared to a similar population of women seen in the clinic who are not part of the study.

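### Both navigator measures stop at follow-up attendance, and the 90-day proportion ignores each woman's due date, although the outcome is named as compliance with recommended follow-up

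*Protocol article*

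**What the plan says.** **The objective and the service.** In the Background, aim 2 is "to determine whether a patient navigator program can improve adherence to follow-up after a diagnosis of an abnormal Pap test". The abstract says the navigator will "provide support and information to promote adherence to follow-up tests, and any necessary surgery or treatment". Under Secondary outcomes, "a secondary outcome is compliance with such recommendations", where the recommendations are those for follow-up of an abnormal Pap test. The same section fixes the end of the service: "Patient navigator contact will cease when the participant has successfully completed follow-up diagnostic care or treatment".

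**The measures.** Secondary outcomes says that what is measured is "the time between diagnosis of the first abnormal Pap test, and attendance at the clinic for follow up". The Statistical analysis section gives two measures:

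- A binary one: "The outcome measure will be determination of follow up for an abnormal Pap smear within 90 days of initial contact by the clinic".
- A time measure, from initial diagnosis to the clinic visit for the follow-up that was recommended. No 90-day limit is stated for it.

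**The comparison.** Navigated women are compared with women who had an abnormal result at the same clinics from 180 to 90 days before the study began, identified from medical records. This comparison is not randomised.

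**The concern.** Compliance with a recommendation has two parts: what was advised, and by when. The stated measures are weak on both.

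1. **The end of the interval.** The service runs to completed work-up or treatment, but neither measure looks past the follow-up visit. A woman who attends and then drops out is still within the navigator's remit, yet she already counts as a success. If navigation mainly helps women finish, the evaluation cannot show it. If it mainly speeds up the first visit without improving completion, the evaluation would overstate what was achieved.
2. **The fixed window.** The 90-day proportion applies the same cut to every abnormal result and is not linked to the recommendation in the woman's record. Any woman whose due date falls later and who keeps it is scored as non-adherent.

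Because the comparator is historical, nothing balances the mix of recommendations between the two groups. A shift in that mix could by itself produce or hide a difference in the 90-day proportion.

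**Working it through.** **The plan's own figures.** The article states no sample size, adherence rate, number of abnormal results or follow-up interval for the navigator comparison, so there is no navigator figure to reproduce. Its sample-size figures (200 randomised and 180 evaluable per arm; 200 × 0.90 = 180) belong to the primary endpoint and do not enter here.

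**Step 1: the texts side by side.**

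| Item | Where it ends |
|---|---|
| Outcome as named (Secondary outcomes) | Compliance with what was recommended |
| Navigator service (Secondary outcomes) | Diagnostic work-up or treatment finished |
| Binary measure (Statistical analysis) | Follow-up within 90 days of clinic contact |
| Time measure (both sections) | Attendance for follow-up |

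The 90-day sentence does not define its event. Read with the time measure beside it, the natural meaning is attendance for follow-up. No row among the measures reaches completion. This conclusion needs no assumed number.

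**Step 2: illustration of scale (all values assumed).** Let Se be the share of truly adherent women scored as 90-day successes, and FP the share of non-adherent women scored as successes, both equal in the two groups. Then

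observed proportion = p × Se + (1 − p) × FP, and observed difference = (Se − FP) × true difference.

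Take true adherence of 0.50 and 0.70, with n per group for a two-sided 0.05 test at 80% power (normal approximation, pooled variance under the null):

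| Se | FP | Observed proportions | Difference | n per group |
|---|---|---|---|---|
| 1.0 | 0 | 0.50, 0.70 | 0.20 | 93 |
| 1.0 | 0.1 | 0.55, 0.73 | 0.18 | 111 |
| 1.0 | 0.3 | 0.65, 0.79 | 0.14 | 161 |
| 0.9 | 0.1 | 0.50, 0.66 | 0.16 | 149 |
| 0.8 | 0.2 | 0.50, 0.62 | 0.12 | 268 |
| 0.6 | 0.3 | 0.45, 0.51 | 0.06 | 1088 |

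The rows with Se = 1 and FP above 0 isolate attendance without completion. The last three rows add the effect of the fixed window.

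**Step 3: the fixed window alone (binary measure only, values assumed).** Let s be the share of women due after 90 days, and suppose none of them attends earlier.

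- Dilution: a 20-point gain among the rest is measured as 20 × (1 − s). This gives 16 points at s = 0.2, 12 at 0.4 and 8 at 0.6.
- Imbalance: if 60% adhere among women due within the window in both groups, the scored proportion is 0.60 × (1 − s). With s = 0.2 in one group and 0.4 in the other, this is 0.48 against 0.36, a 12-point difference with no navigator effect.

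**Step 4: room for longer follow-up.** A control with an abnormal result at the late edge of the historical window has 90 days before the study starts; one at the early edge has 180. A common follow-up of L days that ends before navigation starts needs the late edge at least L days back. The present window therefore allows at most 90 days from the result, taking navigation to start with the study.

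**The case against.** The strongest reply is that the measures suit the aim as worded. Aim 2 speaks of adherence to follow-up, and the abstract states the endpoint as "An evaluation of the patient navigator program as a method to improve adherence and reduce time to follow-up". Treatment and completion appear only in descriptions of the service, and a service may run longer than the endpoint that evaluates it. A uniform window is a legitimate measure of timeliness and matches a historical window that closes 90 days before the study. The article is also condensed, and abstraction rules may sit in the full protocol.

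Much of this stands. Completion is not worded as an endpoint, and a 90-day proportion is defensible as a timeliness measure. It is not a measure of compliance with recommendations, which is the name the article gives the outcome. Nor is the point about a missing detail: the window and the end of the interval are stated.

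Three stronger readings are tempting, and the documents do not support them:

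- A reader might infer that any clinic visit counts. The time measure is worded as attendance for the recommended follow-up, so an unrelated visit would not clearly qualify.
- A reader might infer that women due after 90 days cannot contribute at all. The time measure has no stated limit, so late attenders still contribute their times. The scoring problem is confined to the binary measure.
- A reader might infer that adherent women are often misscored. That needs due dates beyond 90 days, and the documents give none.

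**Conclusion.** The concern holds in a limited form. Both navigator measures end at follow-up attendance, so completion of work-up or treatment is never observed, even though the service is defined by it. This follows from the text alone. The binary measure also applies a window not tied to each woman's recommendation, so it can score an adherent woman as a failure. That is a consequence of the rule as written, but its frequency cannot be determined from the documents. The figures of 16 to 8 points and the spurious 12 points rest entirely on assumed shares of later due dates, an assumed gain and assumed adherence, and on no early attendance by women due later. They show scale and are not estimates.

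The endpoint is secondary, the comparison is historical and no power is claimed for it. The primary endpoint is unaffected. A better definition is worth making because it is inexpensive, and because the control window must be set with the longer follow-up in mind.

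**What to change.** - **Abstraction.** Record the recommended follow-up step and its due date from the medical record in both groups. The time measure already requires the recommended follow-up to be identified. The article does not say whether due dates are always recorded, so report the number without one.
- **90-day proportion.** Keep it, but report it among women whose recorded due date falls within the window, or stratify by recommended interval. This proposes no clinical interval; it uses whatever the record contains.
- **Completion.** Add completion of the recommended diagnostic follow-up or treatment as a further outcome, over the same follow-up length in both groups. Take it from medical records in both, because navigator notes do not exist for the historical women.
- **Control window.** Set it early enough that this follow-up ends before navigation starts.
- **Alternative.** If none of this is adopted, word the aim 2 conclusion as timely first attendance for follow-up, and claim nothing about completed care.

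The cost is a few more abstraction fields, an earlier control window and somewhat longer follow-up before aim 2 can be analysed. Replacing the endpoint outright with individual due dates plus a grace period is possible but debatable, and is not needed to resolve the point.

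### The navigator's 90-day follow-up outcome is timed from clinic contact, while the time outcome is timed from diagnosis; both should start at the abnormal Pap result

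*Protocol article*

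**What the plan says.** Protocol article, Statistical analysis, second paragraph, on the yes/no measure: "determination of follow up for an abnormal Pap smear within 90 days of initial contact by the clinic". The sentence after it reads: "We will compare length of time from initial diagnosis to attendance at the clinic for recommended follow-up".

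The Secondary outcomes section also starts at diagnosis: "The secondary outcome will measure the time between diagnosis of the first abnormal Pap test, and attendance at the clinic for follow up". It names adherence as well: "a secondary outcome is compliance with such recommendations". The Methods/design part of the Abstract lists both goals together: "improve adherence and reduce time to follow-up among participants who receive an abnormal Pap test result".

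The comparison group is historical: "women who received an abnormal Pap smear at the same clinics between 180 and 90 days prior to the start of the study". The navigated group is described in two ways in the same paragraph. It is first all participants with an abnormal smear during the study, each expected to receive a navigator contact. In the closing sentence it is those whom the navigator has contacted. The article does not define the clinic's initial contact, and does not say how a woman who could not be reached is handled.

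**The concern.** Having an adherence measure and a time measure is reasonable. The difficulty is that they start at different events, nothing relates those events to each other, and one of them is a poor origin for evaluating a programme that works by contacting women.

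- Delay between the result and the contact disappears from the 90-day measure, although shortening time to follow-up is a stated goal.
- A woman who is never contacted has no day 0, so the rule as written cannot classify her.
- The start event may differ by group. For historical controls it can only be the clinic's routine contact. For navigated women it could be that contact or the navigator's call, because navigators are drawn from the community partner organizations and the clinic network is one of these.
- Taken literally, the closing sentence selects navigated women on having been reached and applies no such condition to controls.

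At stake is the answer to the study's second aim, whether navigation improves follow-up after an abnormal result.

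**Working it through.** The documents give no sample size, power, delay or time distribution for the navigator comparison, so there is no figure of the plan's own to reproduce. Every delay and distribution below is an assumption, used only to show how the rule behaves.

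**1. What the contact clock leaves out.** Assume 70% of women ever attend, with exponentially distributed time from contact to attendance (mean 60 days), and a fixed delay of L days from result to contact.

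- Within 90 days of contact: 0.70 × (1 − exp(−90/60)) = 0.544, whatever L is.
- Within 90 days of the result: 0.70 × (1 − exp(−(90 − L)/60)).

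| L (days) | From contact | From result |
|---|---|---|
| 0 | 54% | 54% |
| 7 | 54% | 52% |
| 14 | 54% | 50% |
| 30 | 54% | 44% |
| 45 | 54% | 37% |

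**2. Direction of the bias.** Use the same model and let only the delay differ between groups.

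- Navigated women contacted at day 7, controls at day 30: counted from the result, 52.4% − 44.2% = 8.2 points in favour of the navigator; counted from contact, 54.4% − 54.4% = 0. A real gain is hidden.
- Delays the other way round: a real deficit of 8.2 points is hidden.

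**3. Entry conditional on contact.** Let c be the share of navigated women reached, p_r their 90-day proportion and p_u that of women not reached. The proportion among all navigated women is c·p_r + (1 − c)·p_u. Restricting to reached women reports p_r, an error of p_r − [c·p_r + (1 − c)·p_u] = (1 − c)(p_r − p_u). It flatters the navigator if unreached women attend less often and does the opposite if they attend more often. It is zero only if c = 1 or p_r = p_u. The article expects c = 1 but gives no rule if it is not.

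**4. Fit with the control period.** Controls have abnormal results at least 90 days before study start. A 90-day window opened at the result therefore closes on or before study start for every control. A window opened L days later runs past study start for controls whose result came fewer than 90 + L days before it. If results are spread evenly over the 90-day control period, that share is L/90: 14/90 = 16% at 14 days and 30/90 = 33% at 30 days. The control period matches the 90-day window exactly only when the window starts at the result.

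**The case against.** **The clinic's contact and the navigator's contact are different things.** The article uses separate phrases for them, and the clinic's contact must also exist for controls, who had no navigator. On this reading the start event is the clinic's own notification. If its delay is the same in both periods, the clock biases the comparison little. This stands as a plausible reading, but the article does not fix it. Even so, delay before contact is uncounted and an uncontacted woman has no start date.

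**Two measures are not a contradiction.** This stands. Adherence and time are both announced, and the two definitions of time agree with each other. The point concerns only the origin of the 90-day measure and who is counted.

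**Censoring and the choice of test belong in an analysis plan.** This stands, and it limits what can be claimed. A reader might infer that the time comparison will make a good programme look slower. If 50% of controls attend at a mean of 30 days and the navigator adds 10% at a mean of 75 days, the mean among attenders is (0.50 × 30 + 0.10 × 75)/0.60 = 37.5 days against 30. That needs non-attenders to be dropped, which the article neither states nor excludes. It also depends on the inputs: if the early attenders come 10 days sooner, the mean is (0.50 × 20 + 0.10 × 75)/0.60 = 29.2 days.

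**The 90-day measure need not reverse.** A reader might construct a case where 49 of 70 reached controls attend (70%) against 62 of 95 reached navigated women (65%), while among 100 per group the figures are 49% and 62%. That requires the clinic's contact to be something the navigator changes and unreached women to be dropped. The documents establish neither.

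**There is a common horizon.** The yes/no measure has a 90-day window in both groups. That navigator contact continues until care is complete describes the length of the intervention, not of observation.

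**A control window that overruns study start is not contamination.** This stands. Women with results before the study are not described as receiving navigation. Step 4 of the working shows a mismatch with the control period and does not show that controls were navigated.

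**Conclusion.** The point holds in a limited form. The current text starts the navigator's 90-day outcome at an undefined clinic contact, while the time outcome starts at diagnosis. It also describes the navigated group partly by whether the navigator reached the woman. This is a stated rule that measures the second aim badly, so it is more than detail left for later. The bias can go either way and its size cannot be found from the documents. For assumed delays of 7 to 45 days, the contact clock overstates 90-day follow-up from the result by about 2 to 17 points within a group. The comparison is affected only to the extent that delay, start event or entry differs between groups.

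The documents do not support a claim that the endpoint will show harm. An apparent slowing remains possible only if non-attenders are dropped from the time comparison. This is a non-randomized secondary analysis; the randomized comparison of Pap test uptake is untouched. The correction should be made, at that rank.

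**What to change.** In the second paragraph of Statistical analysis:

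- Replace the clinic-contact origin with the date of the abnormal Pap result, in both groups, and state that the time outcome uses the same date.
- Define the navigated group as all women with an abnormal result in the study period, whether or not the navigator reached them.
- Count a woman with no attendance by day 90 as not followed up.
- Keep non-attenders in the time comparison as censored observations.

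The Secondary outcomes section already starts at diagnosis; it need only say that this means the date of the abnormal result.

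The cost is wording. The time outcome already needs this date, so no new data are required. The 90-day proportions will be somewhat lower than when counted from contact, by an amount that depends on the actual delay.

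### The analysis set for navigator time to follow-up is stated inconsistently, and its last wording, taken literally, selects on contact on one side only

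*Protocol article*

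**What the plan says.** All statements are in the protocol article.

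- **Secondary outcomes**, on time from abnormal result to clinic attendance: "Elapsed time in participants assigned to a patient navigator will be compared" with similar clinic patients outside the study. The group is those *assigned*.
- **Statistical analysis**, second paragraph, defining the group: "All participants seen at the study clinics during the course of the study who receive an abnormal Pap smear (intervention population"). The plan is that they "will receive a contact from the patient navigator", and the next sentence sets these same women against the controls. The group is *all with an abnormal result*.
- **Statistical analysis**, last sentence, on the same time outcome: the comparison is made "in the participants who have been contacted by the patient navigator, vs. the control population". The group is those *contacted*.

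The controls are "women who received an abnormal Pap smear at the same clinics between 180 and 90 days prior to the start of the study", a period "when no navigator calls were made (control population) as determined by medical records". No condition on being reached applies to them. The second navigator outcome is binary: "determination of follow up for an abnormal Pap smear within 90 days of initial contact by the clinic". Its clock starts with the clinic's contact, not the navigator's.

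**The concern.** One outcome, time to follow-up, is assigned to differently worded groups in two sections, and the analysis section itself moves from all women with an abnormal result to women contacted. An analyst who follows the last sentence to the letter would remove some women from the navigated side after diagnosis. The historical side would keep everyone.

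Two kinds of women could be lost:

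- **Women the navigator could not reach.** Secondary outcomes lists barriers to care such as work, transport, language and immigration status. It is reasonable to infer, though the article does not say so, that some of these also make a woman harder to reach. Dropping her would make the navigated group look better.
- **Women who attended before the navigator reached them.** The time outcome starts at diagnosis, and navigator contact comes later. A woman who has already attended might never be recorded as contacted. Dropping her removes a short time and makes the navigated group look worse.

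This comparison is the article's evidence for Aim 2, whether a navigator programme improves adherence to follow-up. An estimate that depends on who happened to be contacted would not be the effect of the programme.

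**Working it through.** **No figure to reproduce.** The article gives no sample size, power, effect size, expected contact rate or follow-up rate by reachability for the navigator comparison.

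**Step 1: the three groups side by side.**

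| Place | Group on the navigated side | Includes unreached women? |
|---|---|---|
| Secondary outcomes | assigned to a navigator | yes |
| Statistical analysis, definition | all participants with an abnormal result | yes |
| Statistical analysis, last sentence | those who have been contacted | no, if read literally |
| Historical controls | all with an abnormal result in the window | yes |

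The first two agree with the control side. The third agrees only if every woman is contacted.

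**Step 2: unreached women dropped, no navigator effect (attendance).** Let r be the share reached, and pR and pU the follow-up proportions among reachable and unreachable women.

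- Contacted women: pR
- All historical women: r·pR + (1−r)·pU
- Spurious difference: pR − [r·pR + (1−r)·pU] = (1−r)(pR − pU)

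All three inputs are assumptions. The main illustration takes pR = 0.70 and pU = 0.30 or 0.20. The wider range runs from pR/pU = 0.6/0.4 to 0.8/0.1.

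| r | All-women rate (pU = 0.20 to 0.30) | Spurious difference | Wider range |
|---|---|---|---|
| 1.00 | 70% | 0 | 0 |
| 0.90 | 65-66% | 4-5 points | 2-7 points |
| 0.80 | 60-62% | 8-10 points | 4-14 points |
| 0.70 | 55-58% | 12-15 points | 6-21 points |

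For example, at r = 0.90: 0.10 × (0.70 − 0.30) = 0.04 and 0.10 × (0.70 − 0.20) = 0.05. If pR = pU, the difference is 0 at any r.

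The Background section cites non-adherence of 20% to 90%, so overall follow-up of 10% to 80%. The all-women rates above lie inside that range, but nothing in the article splits it by reachability.

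**Step 3: early attenders dropped, no navigator effect.** Let p be the overall follow-up proportion and e the share who attend before any contact. If those women are excluded, the remaining proportion is (p − e)/(1 − e), and the difference from p is −e(1 − p)/(1 − e). This is negative whenever e > 0 and p < 1. For times the direction is the same: the shortest times leave the navigated side only.

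**Step 4: net direction.** Steps 2 and 3 pull in opposite directions, and the article gives no value for r, e, pR or pU. The sign of the net bias in the time comparison cannot be determined. The figures in Step 2 concern attendance proportions; they show the mechanism and do not measure bias in times.

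**Step 5: with everyone analysed.** If the navigated side is all participants with an abnormal result, contacted or not, both terms vanish at any contact rate.

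**The case against.** The strongest reply is that the paragraph answers itself. It defines the intervention population as all participants with an abnormal result, plans contact for all of them and says these women are the ones compared. Secondary outcomes likewise offers navigation to any participant with an abnormal result. On that plan, assigned, abnormal and contacted name the same women, and the last sentence is only a loose back-reference. Nothing states that unreached women are excluded. A rule for them could also sit in a fuller protocol or analysis plan that is not shown.

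Much of this stands. The absence of a rule for unreached women is not the point here, and the general comparison of all women with abnormal results is not restricted to those reached. What remains is that planned contact for everyone is an intention about delivery, while the sentence that specifies the time analysis names a different group from the one Secondary outcomes names for the same outcome. If contact proves complete, the wordings coincide. If it does not, they give different estimates.

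A reader might go further and infer that the plan compares only women the navigator managed to reach, so that a benefit would appear even if navigation did nothing. The documents do not support that. It overlooks the definition in the same paragraph, it needs incomplete contact that is related to follow-up, and early attenders could push the time result the other way.

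**Conclusion.** The inconsistency is real. The last sentence of Statistical analysis, taken literally, conditions the navigated side on contact while the historical side has no such condition. That *can* bias the Aim 2 estimate; whether it does depends on contact falling below 100% and being related to follow-up, and the net direction for times is unknown.

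The only available size is illustrative and concerns attendance: 0 at full contact, and 4-5 percentage points at 90% reached with assumed attendance of 70% against 20-30%. Lower reach or a wider contrast gives more, as tabulated.

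Severity is moderate. The comparison is secondary, non-randomised and historically controlled. The article bases its judgement of the intervention's success on Pap test compliance alone, and that randomised analysis is unaffected.

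**What to change.** - In the last sentence of Statistical analysis, replace the contacted participants with the intervention population already defined: every participant with an abnormal Pap result, with membership fixed at that result, whether or not the navigator made contact.
- State that this group is used for both the 90-day outcome and the time outcome.
- Align the wording in Secondary outcomes with it.
- Report the share contacted as a process measure, and label any contacted-only analysis as supportive.

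The change is a few sentences and should be settled before the follow-up data are examined. It has two costs. The estimated effect may be smaller, because women who received no navigation stay in the group. Records of follow-up visits are also needed for uncontacted women: Recruitment of participants describes the record-release authorization in terms of verifying screening use, so it should be confirmed that it also covers follow-up visits. The change removes selection on contact only; the comparison remains historical and non-randomised.
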